### Ethics

The study was approved by the research ethics board of Unity Health- St. Michael’s Hospital (SMH REB# 22–186).

## Discussion

Findings of this study, together with data on the clinical outcomes of patients triaged using the two imaging modalities and cost effectiveness analysis should provide a complete assessment of the utility of perfusion CT neuroimaging. If the reliability of decisions made by clinicians is not significantly different between the two neuroimaging protocols, then recommendations regarding neuroimaging in the late time window may need to be modified to reflect these results. Our goal is to determine whether the automated perfusion CT images and quantitative values found in the perfusion CT neurimaging protocol add value to clinical decision making from a reliability standpoint.

Our study is limited to CT neuroimaging and will not tackle cranial MRI—a different imaging modality that may also be used in acute stroke. This will limit the findings of our study as perfusion imaging can also be used with cranial MRIs. Our results will only be applicable to Canadian practice as all our raters are from comprehensive academic centers in this country. As a previous study demonstrated, decision-making is different across the globe even with cases that fit high level recommendations (Level 1A and Level 2B) [46]. Our study also involves some degree of deception of our recruited raters. While we have taken several measures to keep the mechanics of the study confidential, they may still figure out that they are viewing the same cases twice each round. This may lead to efforts towards delivering consistent answers.

Knowledge dissemination will be through presentation in conferences dealing with stroke and neurointervention. Afterwards, the results will be published in peer-reviewed journals.

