**Methods:**

A total of 30 non-consecutive patients will be selected from our institutional database comprising 3144 cranial CT scans performed for acute stroke symptoms January 2018 to August 2022. The clinical and radiologic data of the 30 patients will be presented in random order to a group of 29 physicians in two separate sessions at least three weeks apart. In each session, the physicians will evaluate each patient once with automated perfusion images and once without. We will use non-overlapping 95% confidence intervals and difference in agreement classification as criteria to suggest a difference between the Gwet AC1 statistics (κ_G_).

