**Discussion:**

The results obtained from this study, combined with the clinical outcomes data of patients categorized through the two imaging techniques and a cost-effectiveness analysis, will offer a comprehensive evaluation of the clinical utility of perfusion CT neuroimaging. Should there be no significant disparity in the reliability of decisions made by clinicians using the two neuroimaging protocols, it may be necessary to revise existing recommendations regarding neuroimaging in the later time window to align with these findings.

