### What is the problem and how does our study contribute?

Access to the required advanced neuroimaging may pose a challenge for smaller centers and developing countries. Thus, strict adherence to the AHA guidelines and Canadian Stroke Best Practices may even result in ELVIS patients being denied EVT in centers where advanced neuroimaging is not readily available. In addition, the use of automated CT perfusion imaging also poses a significant financial burden—1.3 million CAD in the first year of its implementation in the province of Ontario and an additional 0.9 million CAD each year thereafter [22]. The incorporation of automated perfusion CT may prove to be a suboptimal allocation of resources, if its routine use fails to yield any discernible improvement in clinical outcomes or influence clinical decision-making.

The impact of automated perfusion CT on specialists’ recommendations regarding EVT for late window ELVIS patients was examined to assess its relevance. If perfusion maps do not significantly alter specialists’ decision-making, their practical utility in clinical practice may be questionable. A previous study demonstrated that addition of automated perfusion CT may result in a lower threshold for an EVT recommendation [23]. However, the study had limited representation of physicians and cases as it only involved two raters from the same center and patients were selected consecutively.

By performing an experimental survey on stroke neurologists and neurointerventionalists with cases that encompass the full gamut of ELVIS, we aim to determine whether the use of perfusion CT neuroimaging (non-contrast CT scan, CTA, and automated perfusion scan) demonstrates better reliability of physicians on repeated surveys (intrarater) and among the physicians of different subspecialties and experience (interrater) compared to non-perfusion CT neuroimaging (non-contrast CT scan and CTA). (See Fig 3) Another objective of the study was to examine the impact the types of neuroimaging protocol on raters’ decision-making, specifically assessing whether the presence or absence of automated CT perfusion images and quantitative values led to an increase or decrease in recommendations for EVT.

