### Sample size

We estimated, using kappaSize package in R version 4.2.0 (R Foundation for Statistical Computing, Vienna, Austria), assuming an anticipated kappa value of 0.6 (substantial), that at least 30 cases were necessary for the lower limit of a 95% two–sided confidence interval to remain above 0.45 between at least 6 raters, considering an anticipated prevalence of EVT recommendation of 0.5 [36]. A rule of thumb for agreement studies with binary outcomes is to have at least 10 raters reviewing at least 30–50 patients [25]. While more patients will enable us to provide an even wider spectrum of patients we also want to avoid rater fatigue. For this study we had 60 cases with three questions each. We need to have at least 6 raters based on our sample size computation but will be aiming for at least 10 to follow the current convention.

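### A non-significant difference in reliability is offered as a reason to reconsider late-window imaging recommendations, but under the stated rule it would not be evidence of similar reliability

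*Protocol article*

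**What the plan says.** The inference appears twice. The Discussion begins its conditional with "If the reliability of decisions made by clinicians is not significantly different between the two neuroimaging protocols, then recommendations regarding neuroimaging" and ends it by saying that, for late presenters, these might have to change. The abstract opens the same argument with "Should there be no significant disparity in the reliability of decisions made by clinicians using the two neuroimaging protocols". In both places the results are to be read together with clinical outcome data and a cost-effectiveness analysis.

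The rule for a difference is in the abstract's Methods and under Agreement statistics: the 95% confidence intervals of the two AC1 values must not overlap, and the level of agreement is considered as well. Under Survey, the same 30 patients are rated by the same physicians with and without perfusion images.

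The Sample size section reports, "assuming an anticipated kappa value of 0.6 (substantial), that at least 30 cases were necessary". The aim of that calculation was "for the lower limit of a 95% two–sided confidence interval to remain above 0.45 between at least 6 raters". It takes EVT to be recommended in half of the ratings. On raters the section adds "We need to have at least 6 raters based on our sample size computation but will be aiming for at least 10"; the abstract says the cases "will be presented in random order to a group of 29 physicians in two separate sessions at least three weeks apart".

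On scope, the Introduction promises "cases that encompass the full gamut of ELVIS". Case selection requires a mismatch ratio of at least 1.8 and a penumbra of at least 15 cc, and excludes poor-quality perfusion studies.

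**The concern.** The study questions ask whether reliability differs, but the practical message is attached to not finding a difference. That message is safe only if the study would probably have found a difference worth caring about, or if the interval for the difference is narrow enough to exclude one. The article offers neither. Its precision target is for one coefficient, and its rule compares two separate intervals.

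At stake is how the headline result will be read. If the rule rarely declares a difference, an imprecise study will look like support for doing without perfusion CT. The error runs mainly one way, towards the reading that could alter recommendations.

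**Working it through.** **Inputs.** Kappa 0.6, lower 95% limit above 0.45, prevalence 0.5, 30 cases, and 6, 10 or 29 raters (Sample size; abstract). Rule: non-overlap of two 95% intervals plus a different class (abstract; Agreement statistics). The article does not define a large difference. I take 0.20, the width of one class on its own scale, as the main example and show others. I take *not significantly different* to mean *not declared different by this rule*, since no other test is stated.

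**The plan's own figure.** For 6 raters, take a mixture model in which a case is unanimous with probability k and otherwise rated by coin flips. The goodness-of-fit sample size is n = χ² / Σ(P₀.₆ − P₀.₄₅)² / P₀.₄₅.
- Each unanimous cell: k/2 + (1−k)/64 = 0.3063 at k = 0.6 and 0.2336 at k = 0.45. The two cells contribute 2 × 0.0727²/0.2336 = 0.0452.
- The other cells contribute (0.15²/0.55) × 62/64 = 0.0396. The sum is 0.0848.
- Two-sided 95%: 3.841/0.0848 = 45.3, so 46 cases. One-sided 95%: 2.706/0.0848 = 31.9, so 32.
- A beta-binomial model gives 38 and 27.

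The stated 30 is close to the one-sided versions. The R package named in the plan was not run, so this is only a side observation. What matters here is that the calculation concerns one kappa and contains no difference between two.

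**The rule, by normal approximation.** The planned half-width is 0.60 − 0.45 = 0.15, so SE = 0.15/1.96 = 0.0765. Two such intervals separate only when the estimates differ by 0.15 + 0.15 = 0.30. The SD of the difference is 0.0765 × √(2(1−ρ)): 0.108 at ρ = 0 and 0.0765 at ρ = 0.5. The chance of separation is Φ((d − 0.30)/SD):

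| True difference d | Declared different (ρ = 0.5 to 0) |
|---|---|
| 0.15 | 2-8% |
| 0.20 | 10-18% |
| 0.25 | 26-32% |
| 0.30 | 50% |
| 0.40 | 82-90% (higher value at ρ = 0.5) |

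A direct interval for the difference needs only 1.96 × SD, which is 0.212 at ρ = 0 and 0.150 at ρ = 0.5. It detects 0.20 in 46% and 74% of studies.

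**The rule, by simulation.** 30 paired cases; AC1 with linearised variance and t intervals; beta-binomial and mixture models; several case correlations.

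| Raters | Rule detects 0.20 | Rule detects 0.30 | Paired 95% CI detects 0.20 (beta-binomial) |
|---|---|---|---|
| 6 | 3-15% | 19-35% | 36-60% |
| 10 | 2-19% | 23-47% | 44-75% |
| 29 | 2-24% | 24-67% | 56-95% |

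- With 29 raters, 0.20 is missed in 100 − 24 = 76% to 100 − 2 = 98% of studies. A beta-binomial run at 0.61 v 0.81 gives 76-83% missed.
- Other 29-rater runs near 0.30 detect more: 74% at 0.57 v 0.28, and 74-79% at 0.6 v 0.9. A difference of 0.40 is usually found (60-96% across runs).
- With no true difference, the rule declares one in at most 0.5% of studies.
- The gain from pairing depends on the cases being linked across protocols. In mixture runs with 29 raters, the paired interval detects 0.20 in 31-38% if they are unlinked and 80-82% if fully linked.
- For one rater's intrarater AC1 (30 cases read twice), the rule detects 0.20 in 3-6% and 0.40 in 22%.

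**Scope.** Total/core ≥ 1.8 means penumbra ≥ 0.8 × core, so every case with a core above 100 cc has more than 80 cc of penumbra. The illustration in Fig 2 has a ratio of 209/130 = 1.61 and would not qualify. Low-mismatch and uninterpretable perfusion results are outside what raters see.

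**The case against.** A fair defence has four parts.

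**Hedging.** Recommendations *may* need modifying, other evidence is to be weighed, and the rule only suggests a potential difference. A reader might infer that a null result automatically triggers a change; the text does not say so. This stands and limits the point. It does not remove it, because the condition is still the absence of a significant difference.

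**Size.** A reader might infer that the study would miss any large difference. The calculations do not support that: around 0.30 with 29 raters the answer depends on the model, and 0.40 would usually be found. The claim is firm for 0.20 and, in the runs made, holds at 0.25 (35-41% detected with 29 raters).

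**Missing detail.** A margin or an interval for the difference could sit in a fuller document, so its absence alone would be no finding. That is right. The fault is that the article itself fixes both the rule and the inference, and the two do not fit.

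**Case mix.** A reader might infer that the case set is concealed or wrongly chosen. It is neither: the mismatch and penumbra criteria are listed and explained under Case selection, which describes the intended breadth as a range of core sizes. What remains is one loose phrase in the Introduction and a conclusion that does not repeat the restriction.

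**Conclusion.** The point holds in a limited form. Failing to declare a difference under the stated rule is not evidence of similar reliability, and the abstract and Discussion should not build on it as if it were. With 29 raters, a true AC1 difference of one agreement class (0.20) goes undeclared in at least about three quarters of studies (76-98%); with 6 or 10 raters the rule does no better. Extra raters help little because the 30 cases limit precision, and ignoring the pairing loses much of the information available. Rating model and case correlation are assumptions, hence the ranges. The figures do not show that perfusion CT improves reliability, nor that the study cannot detect anything. The scope issue is a secondary wording matter.

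**What to change.** 1. Under Agreement statistics, add the AC1 difference between protocols with a 95% confidence interval that respects the pairing, for example a bootstrap that resamples cases and keeps both protocols' ratings of a case together.
2. In the abstract and the Discussion, replace the sentence: a non-significant result is called inconclusive and reported with that interval.
3. Claim similar reliability only if the interval lies wholly within a margin that the investigators justify and fix before the ratings are analysed. The margin should be smaller than any difference they regard as important, so ±0.20 should not be adopted by default: it is the very difference whose non-detection is the problem here.
4. Limit the conclusion to late-window cases like those selected (mismatch ratio at least 1.8, penumbra at least 15 cc, interpretable perfusion). In the Introduction, replace the phrase "cases that encompass the full gamut of ELVIS" with the narrower description under Case selection, which refers to the range of core sizes.

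**Cost.** No new cases or raters; a small amount of extra analysis. The real price is that inconclusive becomes a likely result. With both coefficients at 0.6, the expected half-width of the paired 95% interval is about 0.11-0.19 with 29 raters, 0.15-0.22 with 10 and 0.18-0.24 with 6 (beta-binomial), so a margin of 0.10 could not normally be met. Even at 0.20, used only as an illustration, 29 raters and no true difference would put the whole interval inside the margin in only about 5-89% of studies, depending on case correlation.
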